## Sample Size Calculation

This is a retrospective, non-CTIMP cohort study and randomization or related processes are not applicable. As of 4^th^ May 2020, there have been 311 cases of acute kidney injury in UHDB NHS Trust

## Statistical Analysis

### Summary of Baseline Data and Flow of Patients

Descriptive statistics will be presented to summarize the distribution of baseline variables across each of the groups. The continuous baseline variables will be reported with means & 95% confidence intervals (95% CI), if shown to be normally distributed will be reported with medians & Interquartile Ranges (IQR). The categorical variables will be reported with frequencies & percentages.

### Outcome Analysis

Univariate analysis will be performed to ascertain any significant association of baseline variables with mortality in patients with COVID-19 disease. Any variables with significant association in univariate analysis will be entered in multivariable logistic regression analysis to ascertain the effects of age, gender, ethnicity, comorbidities, medications, use of critical care and acute kidney injury on the likelihood of in-hospital death. A multivariable logistic regression will be performed to ascertain the effects of variable found to be significant in univariate analysis on AKI as an outcome in COVID-19 disease. All tests will be two-tailed, and p<0.05 will be considered significant. Analysis will be performed on IBM SPSS Statistics for Mac, Version 24.0

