# STATISTICS AND DATA ANALYSIS

Descriptive analysis, percentages and 95% Confidence Intervals will be used initially for estimating the incidence of acute kidney injury in COVID-19 positive patients. Chi-squared or Fisher’s Exact tests will also be performed for categorical variables. Multivariable logistic regression analysis will be used to assess the impact of various baseline variables on acute kidney injury and secondary outcomes including mortality.

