### Analysis Groups

Descriptive analysis will be performed in patients with COVID-19 disease between patients who didn’t have AKI with those who had AKI in COVID-19 disease, between AKI in COVID-19 disease and a control group of patients with AKI with no COVID-19 disease and between survivors and non-survivors in COVID-19 disease. For this, categorical variables will be described as frequency and percentages. Continuous variables will be described as mean with standard deviation or median with inter-quartile range. Means for continuous variable will be compared using t-test if the data is normally distributed otherwise Mann Whitney test will be used. Proportion from categorical variables will be compared with chi square test.

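### Both multivariable models choose covariates by univariate p<0.05: this conflicts with the mortality model's stated aim and leaves the AKI model's screening outcome unclear

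*Protocol*

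**What the plan says.** Section 9 states that multivariable logistic regression will "assess the impact of various baseline variables on acute kidney injury and secondary outcomes", mortality among them. Section 9.2.2 (Outcome Analysis) gives the rule for building the models.

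- **Screen.** "Univariate analysis will be performed to ascertain any significant association of baseline variables with mortality in patients with COVID-19 disease". This is the only univariate screen written out in that section.
- **Mortality model.** "Any variables with significant association in univariate analysis will be entered in multivariable logistic regression analysis". The same sentence gives the model's purpose: to estimate the effects on in-hospital death of age, gender, ethnic group, comorbidity, medication, critical care use and AKI.
- **AKI model.** A second logistic regression is to estimate "the effects of variable found to be significant in univariate analysis on AKI as an outcome in COVID-19 disease".
- **Threshold.** "All tests will be two-tailed, and p<0.05 will be considered significant". No separate entry threshold is given.

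Section 9.2.4 (Analysis Groups) adds a descriptive comparison, among COVID-19 patients, of those without AKI "with those who had AKI in COVID-19 disease". It uses a t-test or Mann-Whitney test for continuous variables, and for the rest: "Proportion from categorical variables will be compared with chi square test". It is not named as the screen for any model.

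**The concern.** A univariate p-value does not tell an analyst whether a variable should be adjusted for. A confounder masked in the crude comparison is lost, a real but uncommon factor is lost for want of power, and the final intervals and p-values are reported as if the model had been fixed in advance.

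Two features of the text add to this. In the mortality model, the list of effects to be estimated and the entry rule cannot both be honoured if any listed variable misses p<0.05. In the AKI model, two analysts could read the same sentence and build different models for the study's primary outcome.

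What is at stake is the secondary objective (patient characteristics and outcomes) and the risk-factor analysis for AKI. Ethnicity is an obvious casualty: the limitations in section 12.1 note that the local Black population may be a low proportion, and low-prevalence exposures are the ones a significance gate tends to remove.

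**Working it through.** The protocol gives no power, effect size or events-per-variable figure, and the 330 has no derivation. There is therefore nothing to reproduce, and the figures below are illustrations.

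**Inputs from the protocol**
- 330 AKI patients planned (Study Summary), not split by COVID-19 status.
- AKI incidence in COVID-19 of 5% to 29% (Background).
- Two-sided 0.05 (section 9.2.2).

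**Assumptions**
- All 330 are COVID-positive, or alternatively only 165 are.
- A binary factor with true odds ratio (OR) 1.5 and prevalence 20%, 10% or 5%.
- AKI risk of 0.29 in patients without the factor.

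**1. Screen against AKI**

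N = 330/0.29 = 1,138. Odds without the factor are 0.29/0.71 = 0.4085. Multiplied by 1.5 this is 0.6127, so the risk with the factor is 0.6127/1.6127 = 0.380. The difference is d = 0.090.

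Power = Φ[(d − 1.96·SE0)/SE1], where SE0 = √{p̄(1−p̄)(1/n1+1/n0)} and SE1 = √{p1(1−p1)/n1 + p0(1−p0)/n0}.

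At 20% prevalence, n1 = 228, n0 = 910 and p̄ = 0.308, so SE0 = 0.0342 and SE1 = 0.0355. Power = Φ(0.64) = 0.74, and the factor is dropped 26% of the time.

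| Prevalence | Dropped, 330 cases (N = 1,138) | Dropped, 165 cases (N = 569) |
|---|---|---|
| 20% | 26% | 54% |
| 10% | 49% | 70% |
| 5% | 68% | 81% |

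**2. Sensitivity**
- Holding overall AKI risk, not reference-group risk, at 29% changes the 330-case column to 27%, 49% and 68%.
- Fixing the factor's prevalence among patients without AKI gives 24%, 46% and 65% at 29% incidence. At 5% incidence (N = 330/0.05 = 6,600) it gives 13%, 32% and 53%.
- On that same basis, a factor with OR 2.0 and 330 cases is dropped 0% to 22% of the time across the two incidences.

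**3. Screen against mortality, if that reading applied**

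Assume N = 1,138, prevalence 20%, AKI risk 0.25 without the factor, AKI OR 1.8, 20% mortality without AKI, and an AKI–death OR of 3.

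- AKI risk with the factor is 0.375. Mortality with AKI is 0.75/1.75 = 0.429.
- If the factor acts on death only through AKI, mortality is 0.2 + 0.229×0.25 = 0.257 without it and 0.2 + 0.229×0.375 = 0.286 with it. The induced OR is 1.16.
- By the formula in step 1, the factor passes an AKI screen 96% of the time and a mortality screen 15% of the time.
- With a direct effect on death of OR 1.25, 1.5 or 1.8, the mortality-screen pass rate rises to about 60%, 91% or 99%.

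**4. Room for a fixed list**

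Taking 10 to 20 events per parameter as an assumed rule of thumb, 330 AKI events carry 330/20 = 16 to 330/10 = 33 parameters, and 165 carry 8 to 16. The protocol gives no count of deaths, so the same sum cannot be done for the mortality model.

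**The case against.** A reader might infer that the mortality screen governs the AKI model, so that the AKI model is bound to lose real AKI risk factors. The text does not support that. The words "variable found to be significant in univariate analysis on AKI as an outcome in COVID-19 disease" can mean variables significant in a univariate analysis on AKI, and section 9.2.4 plans tests of AKI against no AKI. The other reading, effects on AKI of the variables just screened, is equally open. What stands is the ambiguity. Loss of a real factor is a risk, not a certainty.

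The contrast of 15% with 96% needs both the disputed reading and an effect on death solely through AKI. With a strong direct effect on death it disappears, so it cannot serve as the size of the problem.

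The conflict between aim and entry rule belongs to the mortality model only. The named list, which includes AKI itself, is tied to in-hospital death, and no covariates are named for the AKI model.

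The 330 may not all be COVID-positive, since section 9.2.4 includes COVID-negative AKI controls, and they are not deaths. It therefore cannot be said outright that there are enough events to make variable reduction unnecessary.

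Lastly, the primary objective is descriptive, and incidence is estimated by percentages with 95% confidence intervals, which screening does not touch. That lowers the severity. A separate analysis plan might list covariates, but the protocol itself commits to the selection rule, so the point is not mere silence.

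**Conclusion.** The point holds in this form. Both models are committed to univariate p<0.05 selection with nothing forced in. In the mortality model this contradicts the stated purpose. In the AKI model the outcome of the screen is not fixed.

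Under the more favourable reading, a screen against AKI, the chance of dropping a real OR 1.5 factor is about 26% to 68% with 330 COVID-positive AKI cases and about 54% to 81% with 165, for prevalences from 20% down to 5%. These figures rest on an assumed effect size, prevalence and COVID split, and on AKI risk at the top of the protocol's range; lower incidence or a larger effect reduces them. A mortality screen would lose more of the factors that act mainly through AKI, by an amount that depends on their direct effect on death.

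Severity: should-fix.

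**What to change.** Replace the entry rule in section 9.2.2 with a pre-specified covariate list for each model, entered regardless of univariate p-value.

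- **Mortality model:** the variables that section already names, including AKI and critical care use.
- **AKI model:** the baseline subset of that list, namely age, gender, ethnic group, comorbidity and medication.
- **Size of each list:** set it against that model's own event count, meaning deaths for the first and COVID-positive AKI cases for the second. State both counts.
- **Univariate results:** report them as descriptive columns only.

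If a screen is kept for the AKI model, the minimum change is to state that it is run against AKI.

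The cost is a change of wording, with the same data and software. The statistical price is slightly wider intervals from a few covariates that turn out to matter little.

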# STUDY SUMMARY

| **Study Title:** | Acute Kidney Injury In COVID-19 in Derby, United Kingdom |
| --- | --- |
| **Local Study Reference:** | UHDB/2020/050 |
| **Study Design:** | Retrospective cohort study |
| **Study Participants:** | All patients suspected of COVID-19 admitted to UHDB NHS Trust between |
| **Planner Number of Sites:** | 1 |
| **Planned Sample Size:** | 330 AKI patients |
| **Planned Start Date:** | 13th May 2020 |
| **Planned Study End Date:** | 31^st^ May 2021 |
| **Research Question/ Aims:** | Epidemiology of COVID-19 patients who developed AKI in hospitalised patients in Derby, United Kingdom. |

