## Outcome

The primary outcome is acute kidney injury in patients with COVID-19 disease.

Secondary outcomes will include all-cause mortality, need for ventilatory support, admission to ICU, length of stay.

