# STUDY PROCEDURES

## Recruitment

### Patient Identification

As this is retrospective cohort study, patients will be identified from microbiology dataset which contains details of nasal and pharyngeal swabs sent for real time reverse transcriptase polymerase chain reaction (RT-PCR) for COVID-19.

Eligible patients will be identified from the hospital dataset, if they had COVID swabs sent for RT-PCR. The data in the microbiology dataset will be linked to hospital electronic patient records containing demographic details to obtain identifiable personal information. The dataset will be linked to other data sources like laboratory information management system, electronic patient prescribing and critical care minimum dataset.

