# DISSEMINATION POLICY

## Dissemination Policy

The data is owned by UHDB NHS Trust and on completion of the study, the data will be analysed and tabulated and a Final Study Report prepared.

- The full study report can be accessed from the chief investigator.
- Participating investigators will have rights to publish any of the study data after discussion with the chief investigator.
- UHDB NHS Trust who sponsored the study will be acknowledged within the publications.
- The study protocol, full study report, pseudo-anonymised participant level dataset, and statistical code for generating the results will be made publicly available on clinicaltrials.gov after ethics approval.
- The study will be reported using the STROBE checklist for observational studies
- Limitation of the study includes –
  - Retrospective nature of the study
  - No urinary chemistry will be available
  - Sampling bias as ethnicity in Derbyshire & Staffordshire may have lower proportion of black population and the results may not be generalizable to other areas
  - Long-term effect of COVID-19 on AKI wont be available
  - Unmeasured confounders was dealt with COVID negative AKI control group where exposure to COVID-19 is not expected to be related to the outcome. This would address the potential magnitude of uncontrolled confounding

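### The terms named for the in-hospital death model include no measure of illness severity at admission, so the AKI-death odds ratio is confounded and probably inflated

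*Protocol*

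**What the plan says.** Section 9.2.2 of the protocol sets up the death analysis in two steps. First, "Univariate analysis will be performed to ascertain any significant association of baseline variables with mortality in patients with COVID-19 disease". Then, "Any variables with significant association in univariate analysis will be entered in multivariable logistic regression analysis", in order to "ascertain the effects of age, gender, ethnicity, comorbidities, medications, use of critical care and acute kidney injury on the likelihood of in-hospital death". The threshold follows: "All tests will be two-tailed, and p<0.05 will be considered significant". The protocol does not list the baseline variables that will be screened.

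Three other sections bear on the point:

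- **Section 3.2 (Outcome)** puts critical care among the outcomes: "Secondary outcomes will include all-cause mortality, need for ventilatory support, admission to ICU, length of stay".
- **Section 7.1.1 (Patient Identification)** describes the data at hand: "The dataset will be linked to other data sources like laboratory information management system, electronic patient prescribing and critical care minimum dataset". Section 8.3 repeats the linkage. Neither limits which laboratory results may be used.
- **Section 12.1 (Dissemination Policy)** states how residual confounding is handled: "Unmeasured confounders was dealt with COVID negative AKI control group where exposure to COVID-19 is not expected to be related to the outcome".

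No section names an admission severity score, admission physiology, oxygen requirement or admission blood result as a covariate.

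**The concern.** A patient who arrives severely ill is more likely to develop AKI and more likely to die. If the model does not hold that initial severity constant, the AKI coefficient carries part of the severity effect, and a larger sample does not remove this.

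The named terms do not fill the gap. Age, gender, ethnicity, comorbidities and medications describe the patient before the acute illness. Use of critical care is related to severity, but it is decided after admission, can follow AKI, and is an outcome elsewhere in the protocol.

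At stake is how the AKI odds ratio will be read. The background section says it is not yet clear how COVID-19 affects outcomes after AKI. An adjusted odds ratio described as an effect will be taken as evidence on that question, although part of it, possibly a large part, may be admission severity.

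**Working it through.** **1. Is there a figure in the plan to reproduce?** No. The protocol gives no assumed AKI-death odds ratio, event rate or severity association. The omission is read from the text, and its size can only be illustrated.

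**2. Can admission severity reach the model?**

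| Route | What the protocol fixes | Does it control admission severity? |
|---|---|---|
| Named terms (9.2.2) | Demographics, comorbidities, medications, critical care, AKI | No named term measures it |
| Screened baseline variables (9.2.2) | Pool not listed; entry needs p<0.05 univariately | Only by chance of listing and screening |
| Use of critical care (9.2.2) | Arises after admission; ICU admission is an outcome in 3.2 | Partial proxy, and possibly on the path from AKI to death |
| COVID-negative AKI group (12.1) | Every member has AKI | No: it holds no AKI versus no-AKI contrast, so it cannot separate AKI from severity in COVID-19 patients |

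**3. How large could the bias be?** All inputs here are assumptions, none from the documents. Simulation with n = 400,000:

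- S ~ N(0,1) is admission severity.
- logit P(AKI) = -1.3 + b·S, giving AKI in about 23-25%.
- logit P(death) = -1.2 + b·S + log(OR)·AKI, with true OR = 1.0 and b = 0.5, 0.8 or 1.0.
- Critical care in about 12%, with log-odds rising 1.1 per SD of S and 0.7 with AKI.
- Noisy admission marker M = S + N(0, 0.7²), reliability 1/(1 + 0.49) = 0.67.

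Estimated AKI-death odds ratio when the truth is 1.0:

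| Model | b = 0.5 | b = 0.8 | b = 1.0 |
|---|---|---|---|
| AKI only | 1.26 | 1.66 | 2.11 |
| AKI + critical care | 1.19 | 1.50 | 1.86 |
| AKI + critical care + noisy marker | 1.07 | 1.17 | 1.30 |

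Repeat runs move these values by a few hundredths. Adjusting for S itself returns about 1.0. Because the true odds ratio is 1.0, the departures reflect confounding and not the non-collapsibility of the odds ratio.

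**4. Share of the bias removed, on the log scale, at b = 0.8.** ln 1.66 = 0.507, ln 1.50 = 0.405, ln 1.17 = 0.157.

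- Critical care alone removes (0.507 - 0.405)/0.507 = 20%.
- Critical care plus the noisy marker removes (0.507 - 0.157)/0.507 = 69%.

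The same sums give 25% and 71% at b = 0.5, and 17% and 65% at b = 1.0.

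**5. Sensitivity.**

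- *Other covariates help.* If the other named covariates captured 40% of the severity variance (assumed), the model with critical care gives about 1.12, 1.34 and 1.49.
- *Wider severity effects.* A separate grid used AKI 25%, death 30%, critical care 12%, severity-AKI odds ratios of 1.5 to 5 per SD and severity-death odds ratios of 2 to 5 per SD. With critical care in the model, a true 1.0 appears as 1.2 to 3.3 and a true 2.0 as 2.2 to 5.8. Adding severity returns 0.96 to 1.03 and 1.93 to 2.08.

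The shift is upward in every scenario.

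**The case against.** The strongest reply is that the list in section 9.2.2 is not stated to be closed. Any screened baseline variable with a significant association is to be entered, the laboratory system is linked without restriction, and a fuller covariate list is commonly left to a statistical analysis plan, which is not at hand. That stands as far as it goes. A reader might infer that the model will contain no severity measure at all, or that the laboratory link serves only to supply creatinine; the protocol says neither. What remains is that it commits to no such measure and makes entry depend on a univariate p-value, which does not select confounders.

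Second, the primary objective is descriptive and the secondary objective in section 3.1 speaks of association. Section 9.2.2 applies the word effects equally to age and gender, as ordinary regression language. This also stands. It limits the seriousness of the point, and changing the wording is part of the remedy. But section 12.1 goes further and says unmeasured confounding was dealt with, which is not true of this estimate.

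Third, the simulation leaves out age and comorbidity, which would absorb some of the bias, and adjusting for critical care may lower the AKI coefficient by blocking a path through it. Both are fair. The 40% scenario shows a smaller bias, still upward.

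Fourth, nothing in the documents shows that particular first-day bloods were measured routinely or capture severity well. That is a reason to check retrievability before choosing markers.

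**Conclusion.** The concern holds for what the protocol names and commits to. The AKI-death odds ratio from section 9.2.2 is confounded by admission severity and probably too high. Neither use of critical care nor the COVID-negative AKI group removes this.

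The size is unknown. Under severity effects of 0.5 to 1.0 log-odds per SD on both AKI and death, a null AKI effect appears as about 1.2 to 1.9 with critical care in the model and before age and comorbidity adjustment. A noisy admission marker brings it to about 1.1 to 1.3. The upward direction rests on severity raising the risk of both AKI and death.

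A reader might go further and infer that the odds ratio would mostly reflect severity. The documents give no severity association from which to judge that, and the assumed range runs from a slight distortion to most of the estimate. The point touches a secondary objective and leaves the descriptive estimate of AKI incidence unaffected. It should be corrected, but it does not undermine the study.

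**What to change.** In section 9.2.2:

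1. Prespecify two or three admission markers, taken as the first value within 24 hours of admission and retrievable from the linked laboratory system. C-reactive protein, lymphocyte count and albumin are examples, subject to checking availability. Leave out markers that are themselves consequences of AKI, such as urea and potassium.
2. Force them into the death model as continuous terms whatever their univariate p-value.
3. Do not rely on use of critical care as the severity adjustment.
4. Report the AKI odds ratio with and without the markers on the same patients, with the number analysed, and describe it as an association.

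In section 12.1, replace the statement that unmeasured confounding was dealt with. Say that the COVID-negative AKI group does not address confounding of AKI and death by severity among COVID-19 patients. If no suitable markers can be retrieved, the association wording and this correction should still be made.

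The cost is a few more columns in an extract already planned and two or three model terms. There are two real downsides. Section 9.3 plans no imputation, so every patient missing a marker drops out of the adjusted model; this is why both estimates need the same patients and a stated number. Markers taken after AKI has begun may also over-adjust slightly.

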### Interim Analysis and Criteria for the Premature Termination of the Study

This is not applicable to a retrospective cohort study

### Analysis Groups

Descriptive analysis will be performed in patients with COVID-19 disease between patients who didn’t have AKI with those who had AKI in COVID-19 disease, between AKI in COVID-19 disease and a control group of patients with AKI with no COVID-19 disease and between survivors and non-survivors in COVID-19 disease. For this, categorical variables will be described as frequency and percentages. Continuous variables will be described as mean with standard deviation or median with inter-quartile range. Means for continuous variable will be compared using t-test if the data is normally distributed otherwise Mann Whitney test will be used. Proportion from categorical variables will be compared with chi square test.

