**STUDY PROTOCOL**

# BACKGROUND

On 31^st^ December 2019, a cluster of pneumonia cases were detected in Hubei province of China where the cause was unclear. The cause for these cases was subsequently identified as a virus which was referred to as SARS-CoV-2, and the associated disease as COVID-19.^1^ This evolved rapidly into a global pandemic with first case reported in UK as early as on 30^th^ January 2020.^2^ As of 30^th^ April 2020, there have been 3.05 million laboratory confirmed cases world-wide with 161,145 cases in United Kingdom in 539,768 cases tested for COVID-19.^3^ The epidemiology of COVID-19 has differed in China, US and Italy which have different demographic characteristics, testing methods and different ways to curb the spread of infection which can be altered by many things, including behaviour, and the stringent social distancing measure.^4-7^ Though the pandemic started in China, as of 30^th^ April 2020, it has reported only 58.32 cases per million people (pmp) as compared to United kingdom which has reported 2433.8 cases pmp.^3^ This has resulted in different epidemiology of COVID-19 and organ system involvement. Lung involvement in the form of alveolar haemorrhages and respiratory failure has been well document in patients with COVID-19 and has been focus of attention, however, other organs are also affected in COVID-19, but there has been limited information kidney involvement in COVID patients.^5,8^ In initial reports, the acute kidney injury (AKI) incidence in COVID-19 has ranged from 5% to 29% with substantial variation between centres,

possibly due to differences in population demographics and risk factors for AKI.^1,2,5-7^ Initial reports on a small number of patients suggest that SARS-CoV-2 may have a specific effect on the kidneys but it is not yet clear to what extent COVID-19 increases the risk of AKI or how COVID-19 impacts outcomes after AKI.^8,9^

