# OBJECTIVES AND OUTCOME MEASURES/ ENDPOINTS

## Objectives

Primary objective

The primary objective is to describe the epidemiology of acute kidney injury associated with COVID-19 in patients admitted to hospital.

Secondary objectives:

To investigate the association between patient characteristics and patient outcomes in patients admitted with COVID-19.

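### The comparison of AKI with and without COVID-19 is planned only as crude tests, so it cannot separate COVID-19 from case mix or do the confounding control claimed for it

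*Protocol*

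**What the plan says.** The Background ends with two unknowns: how far COVID-19 raises the risk of AKI, and "how COVID-19 impacts outcomes after AKI". The second is not carried into section 3.1, where the secondary objective is "To investigate the association between patient characteristics and patient outcomes in patients admitted with COVID-19".

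Section 9.2.4 (Analysis Groups) lists three descriptive contrasts. One is "between AKI in COVID-19 disease and a control group of patients with AKI with no COVID-19 disease". The methods are: "Means for continuous variable will be compared using t-test if the data is normally distributed otherwise Mann Whitney test will be used", and "Proportion from categorical variables will be compared with chi square test". No outcome is named for this contrast, and no matching, stratification or adjustment is given.

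Section 9.2.2 (Outcome Analysis) specifies two regressions. The mortality model is fed by a univariate screen for "any significant association of baseline variables with mortality in patients with COVID-19 disease". The other models AKI as an outcome, also within COVID-19 disease. COVID-19 status is not among the listed covariates. The same section sets a two-sided 0.05 significance level for all tests.

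The opening paragraph of section 9 mentions multivariable logistic regression for AKI and the secondary outcomes, but names neither a pooled population nor a COVID-19 term.

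The limitations in section 12.1 (Dissemination Policy) state that unmeasured confounding was handled by the COVID-negative AKI control group.

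**The concern.** The control group has no use in describing COVID-19 patients alone. Its natural use is to ask whether AKI carries a different prognosis with COVID-19 than without it, which is the Background's second unknown. For that contrast the protocol specifies only unadjusted tests, while its adjusted analyses are placed where the contrast cannot be estimated.

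The two AKI groups may differ in age, ethnicity, comorbidity and reason for admission. A crude test of death between them responds to those differences as well as to COVID-19. Section 12.1 makes this more than a matter of labelling. It credits the control group with handling confounding that was not measured, when the planned tests do not remove even the confounding that was.

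**Working it through.** **Which analysis can estimate a COVID-19 effect among AKI patients?**

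| Section | Population | Method | COVID-19 status estimable? |
|---|---|---|---|
| 9, opening | not stated | logistic regression, in general terms | no such term named |
| 9.2.2, mortality model | COVID-19 patients | logistic regression | no, it is constant |
| 9.2.2, AKI model | COVID-19 patients | logistic regression | no, it is constant |
| 9.2.4, AKI contrast | AKI with and without COVID-19 | t-test, Mann-Whitney, chi-square | yes, but unadjusted |

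Only the last row contains the contrast, and it has no adjustment.

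**Is there a figure of the plan's own to reproduce?** No. The Study Summary gives 330 AKI patients and section 9.1 gives 311 cases by 4 May 2020. Neither is split by COVID-19 status, and no effect size, mortality or precision target is stated.

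**Illustration, on assumptions only.** None of these rates is in the protocol. Take one binary risk factor, with mortality m0 = 15% in low-risk patients and m1 = 30% or 45% in high-risk patients. COVID-19 has no effect within either stratum, so the stratum-adjusted odds ratio is 1.00. Let q be the high-risk share of a group.

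- Group mortality: p = q × m1 + (1 − q) × m0
- Crude odds ratio: [p_covid / (1 − p_covid)] / [p_control / (1 − p_control)]

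Worked case, with q = 40% in controls, 60% in COVID-19 and m1 = 45%:

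- p_control = 0.40 × 0.45 + 0.60 × 0.15 = 0.27
- p_covid = 0.60 × 0.45 + 0.40 × 0.15 = 0.33
- Crude odds ratio = (0.33/0.67) / (0.27/0.73) = 1.33

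The last column is the chance of p<0.05 in the direction of the imbalance, by the normal approximation for two proportions. It covers control/COVID-19 group sizes of 165/165, 230/100 and 330/330, also assumed. With no imbalance this chance is 2.5%, half of the two-sided 5%.

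| High-risk share, control vs COVID-19 | Crude OR, m1 = 30% | Crude OR, m1 = 45% | Chance of p<0.05 |
|---|---|---|---|
| 45% vs 55% | 1.09 | 1.15 | 5% to 13% |
| 40% vs 60% | 1.19 | 1.33 | 9% to 39% |
| 35% vs 65% | 1.30 | 1.54 | 15% to 71% |

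If the controls are the higher-risk group, the odds ratios invert: 1/1.09 = 0.92 to 1/1.54 = 0.65.

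**The case against.** **The question is not an objective.** This stands. The effect on outcomes after AKI appears only as a gap in the Background. The secondary objective concerns COVID-19 admissions, and regressions within those patients fit it. A reader might infer that a formal objective is left unanswered; section 3.1 does not support that.

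**The contrast is called descriptive.** This also stands. Section 9.2.4 names no outcome for it, so a comparison of deaths is likely but inferred. A reader might go further and conclude that case-mix differences will be published as a COVID-19 effect. The protocol says no such thing. The descriptive label is nevertheless not a full answer, because section 12.1 gives the same control group a confounding-control role.

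**A pooled model is not excluded.** The general sentence opening section 9 would permit one, and a separate statistical analysis plan may exist. But section 9.2.2 already fixes populations and candidate covariates, and neither model specified there can contain a COVID-19 term. The point rests on what is fixed there and on the claim in section 12.1, not on missing detail.

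**Adjustment would not settle causation.** Correct. If COVID-19 itself causes AKI, restricting to AKI patients can link COVID-19 to other causes of AKI that also affect survival. Adjustment for baseline variables need not remove that.

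**Kidney recovery.** A reader might also fault the lack of a renal recovery outcome, since 13 May 2020 to 31 May 2021 is 383 days. The documents do not support this as an error. The later date is the study end, nowhere a follow-up or extraction date, and section 12.1 openly discloses "Long-term effect of COVID-19 on AKI wont be available". An added endpoint or an AKI-by-COVID-19 interaction model would be a preference.

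**Conclusion.** The point holds in a limited form. The only analysis specified for AKI with COVID-19 against AKI without it is unadjusted, and the regressions specified in section 9.2.2 cannot estimate a COVID-19 term. The planned tests therefore cannot deliver what section 12.1 claims for the control group. Any crude outcome difference between the two groups would combine COVID-19 with case mix.

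Neither the size nor the direction of that mixing can be derived from the protocol. The illustrative range shows only that moderate imbalance could matter at group sizes of this order; it rests wholly on assumed stratum mortalities, risk shares and group splits. This merits a change to the analysis section and does not undermine the primary objective of describing AKI in COVID-19.

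**What to change.** 1. Add to section 9.2.2 one multivariable logistic model for in-hospital death in all eligible AKI patients. COVID-19 status is the exposure. The covariates are baseline variables already planned (age, gender, ethnicity and comorbidities), fixed in advance and not chosen by univariate significance.
2. Report the adjusted odds ratio with its 95% confidence interval as an association, stating that residual confounding and selection on AKI remain.
3. Keep the section 9.2.4 tests as description.
4. Replace the section 12.1 statement with one saying that the control group does not remove unmeasured confounding.

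If the sponsor declines the model, the minimum is to declare the contrast purely descriptive and still make change 4.

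The cost is one further model. The covariates are already planned, and swabbed COVID-negative patients are in the source dataset. Section 9.3 allows no imputation, so patients with missing covariates drop out and their number must be reported by group. Pre-admission kidney function depends on earlier creatinine results being available, so it is better added as a sensitivity analysis where a baseline value exists.
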